## **SUMMARY**

**Rationale:** There is no consensus on the use of ACE inhibition in Fontan patients without ventricular dysfunction. Multiple centres prescribe enalapril on a routine base for patients with a Fontan circulation and a preserved ventricular function, while other centres have considerable doubt about its effectiveness. Too little research has been done to the effectiveness of ACE inhibition in Fontan patients. There are as yet no studies available that investigate the effect of ACE inhibition on various cardiovascular parameters in patients with a Fontan circulation. By studying the effect of ACE inhibition on cardiovascular parameters as systolic and diastolic ventricular function, cardiac output, and the sensitivity of the cardiovascular system to fluid changes, the basic effects of ACE inhibition on the cardiovascular system of Fontan patients will become more clear. This will result in a more appropriate selection of patients that will profit of the use of ACE inhibitors.

**Main objective:** To treat Fontan patients for 3 months with the ACE inhibitor enalapril and compare a set of cardiovascular measurements before and after treatment in order to study its effect on the cardiovascular system and the effect of a reversible fluid challenge and depletion in Fontan patients, and to correlate all these results with the results of a symptom limited maximal exercise test.

**Study design:** This study consists of a longitudinal intervention study and a cross-sectional study.

**Study population:** 55 patients with a univentricular heart after palliation with the Fontan circulation will be included from an age of 8 until 18 years old. Patients who already use enalapril will be excluded. A number of fifty healthy age and gender matched subjects will serve as controls.

**Intervention (if applicable):** To all Fontan patients enalapril will be given twice daily at a dose of 0,5 mg/kg/day with a maximum of 20 mg per day. All Fontan patients will undergo all the investigations before and after treatment and healthy controls will undergo all the investigations once, except for blood testing and the symptom limited exercise test which will not be performed in healthy controls.

### **Main study parameters/endpoints:**

- Cardiopulmonary exercise stress test:  $VO_2$ peak.
- Cardiac autonomic nervous activity: heart rate variability and pre-ejection period.
- Outcome of passive leg raising and head up tilt table testing: cardiac output and cardiac autonomic tone.

### **Nature and extent of the burden and risks associated with participation, benefit and group relatedness:**

Patients with a Fontan circulation will have to visit the LUMC twice and these visits will be instead of normal appointments. In the future, Fontan patients could possibly have advantage from this research. For healthy subjects, this research means that they have to come only once to the LUMC. The exams themselves are not harmful to health, will cost three hours per visit and have a low burden. Only venapunction, which only will be done in the group of Fontan patients, can be painful, but we will thrive to soften the pain by using, for example, emla cream.

## **1. Introduction and Rationale**

At present more than 90% of patients with congenital heart disease reach adulthood. However, their life expectancy is less than normal, and many patients suffer from heart failure or pulmonary hypertension (Nieminen et al). A group of patients that is especially prone to these long-term sequelae are patients with a univentricular heart. Although heart failure may be treated medically by anti-heart failure medication, most studies evaluating the effectiveness of these medications are performed in patients with a biventricular circulation.

Patients with a univentricular heart usually undergo a stepwise Fontan procedure. This technique consists of a stepwise approach with first connecting the superior vena cava with the pulmonary arteries and at a later stage connecting the inferior vena cava with the pulmonary arteries, either as an intra-atrial tunnel, or as an extra cardiac conduit (Total Cavopulmonary Connection; TCPC). After Fontan palliation these patients lack a heart chamber that pumps the blood through the pulmonary circulation. Therefore venous pressure is necessary to overcome pulmonary resistance. Any increase in pulmonary vascular resistance will lead to increased central venous pressure and venous congestion. On the other end of the circulation there is downstream decreased flow (Gewillig et al). This results in a critical fluid balance and dependence of cardiac output on adequate preload (La Gerche et al). While a volume challenge can increase cardiac output in patients (De Mey et al), fluid overload can lead to increased central venous pressure, resulting in venous congestion and ascites and pleural effusion, while dehydration immediately has a negative effect on cardiac output and may result in signs of clinical forward failure. In Fontan patients there is a delicate balance between systemic and pulmonary vascular resistance, while systemic circulation is highly preload dependent. In most Fontan patients a fluid challenge resulted in an increase in end-diastolic pressure and an increase in cardiac output as well (De Mey et al). On the other hand, an increase in end-diastolic pressure may have detrimental effects on the Fontan circulation due to a decrease of the transpulmonary gradient.

Fontan patients show a slightly diminished diastolic and systolic ventricular function already 10 years after completion of the TCPC (Bossers et al). During adulthood an increasing number of patients will suffer from clinical signs of ventricular dysfunction (Ohuchi J Cardiol 2016). Furthermore, a decrease in aortic distensibility is now being recognized as an important factor for increased afterload of these ventricles (Ohuchi et al), thereby increasing the process of ventricular deterioration.

Furthermore, the normal mechanisms that can counteract the negative effects of changes in fluid volume have been described to be diminished in Fontan patients as well. The main regulatory mechanisms in healthy individuals to counteract the effects of fluid changes on cardiovascular

parameters are the possibility of the heart to change stroke volume, the autonomic nervous system and the aortic stiffness or aortic distensibility.

#### Ventricular function:

During longer-term follow-up a significant number of patients show impaired ventricular function (Ono et al). When dobutamine stress is used in Fontan patients even those with a normal ventricular function lack the possibility to increase their stroke volume (Robbers-Visser et al). These cardiovascular changes in most patients result in a diminished exercise capacity (Bossers et al 2014).

#### Cardiac autonomic Nervous Activity:

Failure of the autonomic nervous system to adapt to differing circumstances is one of the key markers in the development of heart failure and may result in an increased risk of rhythm disturbances (Dekker et al 1997; La Rovere et al 2001; Nolan et al 1998; Saul et al 1988; Schwartz et al 1992). Assessment of cardiac autonomic function has important clinical implications as cardiac autonomic balance can be positively modified by exercise training (Groehs et al 2015) and a variety of other pharmacological and more invasive measures (Schwartz et al 2015), contributing to improvement of prognosis. Reports in patients with congenital heart disease including Fontan patients have shown a reduction in cardiac autonomic nervous activity, although its relation to symptoms and prognosis remains as yet unclear (Ohuchi et al 2003; Ohuchi et al 2011). In Fontan patients parasympathetic activity seems to be reduced as assessed by the heart rate recovery after cessation of exercise. In addition, various aspects of heart rate variability (HRV) are reduced in Fontan patients, reflecting both parasympathetic as well as sympathetic cardiac autonomic nervous activity (Bossers et al 2015). The clinical value of HRV in Fontan patients has yet to be established, but it has been demonstrated previously that HRV analysis might contribute to early detection of patients who will develop arrhythmias (Dahlqvist et al 2011).

#### Aortic stiffness:

In addition to reduced ventricular function, in many congenital heart disease patients, the vascular function of especially the aortic arch show significant differences from normal (Kojima et al). Several studies have investigated vascular function in Fontan patients. Both in paediatric patients as well as in adult patients arterial stiffness and pulse wave velocity are increased (Tomkiewicz et al; Lambert et al; Biglione et al; Myers et al). However, no clear relation with ventricular function could be made. In the assessment of cardiovascular risk factors the measurement of pulse wave velocity of the aorta has become a key factor. Aortic pulse wave velocity is a surrogate of aortic stiffness.. Since arterial baroreceptors are present in the aortic arch it is understandable from a physiological standpoint that arterial stiffness and cardiac autonomic function have a relationship. Various studies have found a

correlation between cardiovascular autonomic function and indices of arterial stiffness (Chrysohoou et al; Nemes et al).

In the present study we will evaluate 46 patients with functional univentricular hearts after TCPC. A fluid challenge will be given by passive leg raising. Passive leg raising has shown to be an effective and reversible and safe method of studying the effect of a fluid challenge on various cardiovascular parameters (Cherpanath et al). This method is extensively being used in intensive care units to predict the effect of fluid challenge on the circulation of various groups of patients. Depletion of central and splanchnic blood volume will be induced by a passive head-up-tilt test. In a previous study the reduction of portal venous flow is more pronounced in symptomatic Fontan patients (Hsia et al. J Thorac Cardiovasc Surg).

#### Enalapril:

Enalapril, an angiotensin converting enzyme (ACE) inhibitor, has been shown to be effective in reducing mortality in patients with heart failure and reduced systolic function for more than 25 years. In subsequent studies its effectiveness has also been proven in patients with mild to moderate symptomatic heart failure. In recent guidelines ACE inhibition has therefore become the cornerstone of therapeutic interventions in patients with systolic heart failure. The effectiveness of ACE inhibition has been ascribed to its effect on various cardiovascular and pulmonary parameters, including systemic vascular resistance, cardiac autonomic tone (KD Maida et al), aortic pulse wave velocity (PWV) and lung function (Contini et al; Abraham et al). The success of ACE inhibition in patients with systolic heart failure and a biventricular heart has also led to the introduction of ACE inhibition to improve the Fontan circulation in patients with a univentricular heart.

The use of ACE inhibition in patients with a univentricular heart is, however, controversial. There is consensus on the use of ACE inhibition in Fontan patients with ventricular dysfunction. However, many centres also prescribe enalapril on a routine base for patients with a Fontan circulation and a preserved ventricular function, while other centers have considerable doubt about its effectiveness (Wilson et al; Int J Cardiol; Wilson et al Heart Lung and circulation). In a small study no effect of enalapril on exercise capacity in Fontan patients has been found (Kouatli et al, circulation). However, when enalapril is used in univentricular pre-Fontan patients a decrease in end-diastolic pressure (Yim et al Cardiol Young) and a redirection of blood flow to the systemic circulation (Lee et al; Heart 2011) has been found. These cardiovascular effects, however, did not improve somatic growth, ventricular function or heart failure severity score during the first year of life (Hsu et al Circulation 2010).

There are as yet no studies available that investigate the effect of ACE inhibition on various cardiovascular parameters in patients with a Fontan circulation. By studying the effect of ACE inhibition on cardiovascular parameters as systolic and diastolic ventricular function, cardiac output, and the sensitivity of the cardiovascular system to fluid changes the basic effects of ACE inhibition on the cardiovascular system of Fontan patients will become more clear. This will result in a more appropriate selection of patients that will profit most of the use of ACE inhibitors.

## **2. Objectives**

The objectives of the present study are as follows:

- To assess autonomic parasympathetic and sympathetic function as well as vascular function in a population of patients with univentricular hearts palliated by the Fontan procedure and compare it with the results in healthy subjects.
- To assess the effects of central fluid depletion by means of a passive head-up-tilt test and central fluid loading by passive leg raising on cardiac output, aortic distensibility and hepatic venous blood flow patterns in a group of patients with a Fontan circulation and compare it with the results in healthy controls.
- To correlate the above mentioned results with the results of a symptom limited maximal exercise test.
- To treat Fontan patients for 3 months with the ACE inhibitor enalapril and compare a set of cardiovascular measurements before and after treatment in order to study its effect on the cardiovascular system in Fontan patients.
- To study the effect of a reversible fluid challenge and fluid depletion on cardiovascular parameters before and after a period of enalapril treatment in order to study changes in fluid susceptibility in Fontan patients.

### **3. Study design**

In the present study we will compare several cardiovascular measurements (described below at '6. Study parameters') before and after treatment of enalapril, in patients with a univentricular heart after palliation with the Fontan circulation. Patients will start with treatment of enalapril after all cardiovascular measurements at baseline have been performed. After a 3-month period of treatment with enalapril, all cardiovascular measurements will be repeated.

Healthy age and gender matched subjects will serve as controls. All cardiovascular measurements, except for blood testing and cardiopulmonary exercise stress testing, will be performed just once in healthy controls. They will not be treated with enalapril.

#### **4. Study population**

##### Population:

Patients, who have been operated in the Leiden University Medical Centre (LUMC), with a univentricular heart after palliation with the Fontan circulation will be included. We strive for including 55 patients. A number of 55 healthy age and gender matched subjects will serve as controls.

##### Inclusion criteria:

Patients with a univentricular heart after palliation with the Fontan circulation from 8-18 years old.

##### Exclusion criteria:

Patients who already use enalapril.

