##### Sample size calculation:

To detect statistical significant difference of our main study parameter  $VO_2\text{peak}$  (ml/kg/min), between Fontan patients before and after treatment with enalapril, we calculated a group size of 52 will be sufficient. We calculated this sample size for paired observations with a clinical relevant effect of 10% elevation after treatment, with a mean of 33.5 and SD of 6.8 before treatment (Bossers et al.; J Thorac Cardiovasc Surg 2014) and an elevation of the mean to 36.85 with an expected same SD after treatment and calculated a SD of the difference of 6.8 with a correlation coefficient of 0.5. We used an alpha of 0.01 with 80% power. We used a lower alpha of 0.01 to correct for multiple comparison according to the Bonferroni correction, because we have five main study parameters. Moreover, we also need to take the change of drop out into account, which means we need 55 patients per group when we expect a 5% drop out. This means a group size of in total 55 Fontan patients and a group of 55 healthy subjects will be sufficient.

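### The question is about ACE inhibition as a class, but the only exclusion is current enalapril use, so a baseline free of renin-angiotensin blockade is not guaranteed

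*Protocol*

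**What the plan says.** **Question and design.** The Protocol's Summary and Introduction frame the subject as ACE inhibition, a drug class. The treatment objective (section 2) is "To treat Fontan patients for 3 months with the ACE inhibitor enalapril and compare a set of cardiovascular measurements before and after treatment". Sections 3 and 7 make this a within-patient comparison. Healthy controls are untreated, are measured once and have no exercise test.

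**Entry.** Section 4 has one inclusion criterion, "Patients with a univentricular heart after palliation with the Fontan circulation from 8-18 years old", and one exclusion criterion, "Patients who already use enalapril". The Summary repeats the exclusion: "Patients who already use enalapril will be excluded". No section mentions other ACE inhibitors or angiotensin-receptor blockers, either as a bar to entry or as a restricted concomitant drug.

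**Ventricular function.** The Summary opens with "There is no consensus on the use of ACE inhibition in Fontan patients without ventricular dysfunction". The Introduction, under Enalapril, states "There is consensus on the use of ACE inhibition in Fontan patients with ventricular dysfunction" and adds that "many centres also prescribe enalapril on a routine base for patients with a Fontan circulation and a preserved ventricular function", which it describes as controversial. Neither the objectives nor the entry criteria mention ventricular function. Section 6 lists a complete echocardiographic evaluation among the study measurements, and section 3 has all measurements done before treatment starts.

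**Sample size.** For VO2peak, "we calculated a group size of 52 will be sufficient"; this is raised to 55 for dropout.

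**The concern.** In a before-after design without a concurrent untreated group, the baseline measurement is the only comparator. The change estimates the effect of ACE inhibition only if that baseline was taken off drugs with the same action. The exclusion secures this for one drug, whereas the question concerns the class. For a patient already on a related drug, the before-after difference measures something else, probably smaller. The controls cannot correct this: they are measured once, and for VO2peak not at all.

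Two things would be at stake. The estimated mean change would be pulled toward zero, and a calculation with almost no reserve would lose power. A null result could then reflect contaminated baselines rather than an ineffective drug.

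A second, lesser issue concerns who the result speaks for. The rationale locates the doubt in patients with preserved function, but entry is open to any Fontan patient aged 8 to 18 not on enalapril. The Introduction itself describes reduced ventricular function in this population. An overall average therefore need not describe the group whose treatment is said to be in dispute.

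**Working it through.** **1. The text.**

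| Element | Where | Scope |
|---|---|---|
| Subject of study | Summary; Introduction, Enalapril | ACE inhibition (class) |
| Exclusion | Summary; section 4 | Enalapril (one drug) |
| Group in dispute | Summary; Introduction, Enalapril | Preserved ventricular function |
| Objectives | Section 2 | Fontan patients, no limit on function |
| Inclusion | Section 4 | Fontan circulation, 8-18 years, no limit on function |

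The first two rows differ in scope. The third differs from the fourth and fifth, but the fourth and fifth agree with each other.

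**2. The protocol's own sample size.** Inputs from section 4: mean 33.5 before and 36.85 after, SD 6.8 at both times, correlation 0.5, alpha 0.01, power 80%. Sidedness is not stated; two-sided reproduces the figure.

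- Mean difference: 36.85 − 33.5 = 3.35.
- SD of the difference: √(2 × 6.8² × (1 − 0.5)) = 6.8.
- Standardised effect: 3.35 / 6.8 = 0.493.
- Paired t-test with the noncentral t distribution: n = 52, with power 80.5% at 52.
- Dropout: 52 / 0.95 = 54.7, so 55.

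The stated figures reproduce. The margin above 80% is half a percentage point.

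**3. Illustration of dilution.** The documents give no share of patients on a related drug, so the share f is an assumption. Also assumed: those patients show no change at all, the others change by 3.35 on average, and the SD of the change is 6.8 within each group. Then

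- mean change = 3.35 × (1 − f);
- SD of the change = √(6.8² + f(1 − f) × 3.35²), where the second term is the variance added by mixing the two groups;
- power is from the paired t-test at n = 52, two-sided alpha 0.01.

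For f = 0.10: mean change = 3.35 × 0.9 = 3.015; SD = √(46.24 + 0.09 × 11.22) = 6.87; power = 68.6%.

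| Assumed share f | Mean change | SD | Power at 52 | n for 80% |
|---|---|---|---|---|
| 0% | 3.35 | 6.80 | 80.5% | 52 |
| 2% | 3.28 | 6.82 | 78% | 54 |
| 5% | 3.18 | 6.84 | 75% | 58 |
| 10% | 3.02 | 6.87 | 69% | 65 |
| 20% | 2.68 | 6.93 | 55% | 82 |
| 30% | 2.35 | 6.97 | 41% | 107 |

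A partial rather than absent response would give smaller losses.

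**4. Ventricular function.** No comparable calculation is possible. The documents give neither the share of patients with dysfunction nor how their VO2peak would respond, so even the direction of any effect on the average is unknown.

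**The case against.** The strongest reply on the exclusion is that the problem may be empty. Enalapril is the drug that the protocol describes centres prescribing, and nothing suggests that any eligible child takes another ACE inhibitor or a receptor blocker. The shares above are invented, and so is the assumption of no response. All of this stands as a limit on size. It does not remove the gap, because the criterion as written still admits such patients and nothing else in the design would reveal or correct a contaminated baseline.

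On ventricular function the reply is stronger. A reader might infer that the population fails to match the study question. The documents do not support that: the objectives are worded for Fontan patients generally and agree with the entry criteria. Section 8 also hopes to profile those who respond best and least, which a range of function can serve. Restricting entry would be a trade-off at one centre that needs 55 patients.

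Nor do the documents support reading the dysfunction group as one where the answer is settled. The Introduction reports consensus on use, not a known effect on VO2peak, autonomic activity or response to fluid shifts. Some patients with dysfunction may already take enalapril and so be excluded, though untreated ones remain eligible.

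Finally, one might conclude that the trial could say nothing about preserved function. That goes too far, since baseline echocardiography allows the subset to be identified.

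**Conclusion.** The point on the exclusion holds. The question is class-level, the exclusion covers one drug, and the uncontrolled before-after comparison depends entirely on an untreated baseline. The wording permits dilution; it does not show that dilution will occur. If no enrolled patient takes a related drug, the loss is zero. If 2% to 5% do and show no change, VO2peak power is about 78% to 75%. The larger losses, down to 41% at 30%, need shares for which the documents give no basis.

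On ventricular function, the supportable statement is that the enrolled population need not match the rationale. It is a looseness between rationale and eligibility, not a contradiction between objectives and eligibility, and no size or direction can be attached to it.

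**What to change.** 1. Reconcile the exclusion criterion in section 4 and the Summary with the class-level question, so that the baseline is free of renin-angiotensin blockade. One way is to extend the exclusion from enalapril to current use of any ACE inhibitor or angiotensin-receptor blocker. How related drugs are handled clinically is for the investigators to settle. The cost is a short amendment and possibly a few fewer eligible patients at a single centre.

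2. Leave entry open as to ventricular function, but classify patients by the baseline echocardiogram, with a cut-off set by the investigators before the results are seen, and report the preserved-function subset alongside the whole group. This needs no extra measurement. Its cost is precision: the subset will be smaller than the 52 on which the power calculation rests, so its estimate should be given with a confidence interval and not judged by significance alone.
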